**Table 3 Tab3:** **Handling of loss to follow-up**

**Level**	**Reason**	**Consequence**
Tooth	Complication	Complications leading to tooth loss will be counted as non-survival. Teeth with complications which allow the retention of the tooth will be count as non-success. Required follow-up treatments will be recorded and survived teeth will be followed up on.
	Lesion treated by other dentist	Tooth will be counted as non-success or non-survival.
	Tooth exfoliation	The last observation will be carried forward.
Patient	Adverse or serious adverse events related to treatment or material	Counteractive measures will be taken and events documented.
		Patient and tooth will be censored and the last observation carried forward.
	The patient cannot be examined (lost to follow-up)	Patient and survived tooth or teeth will be censored and the last observation carried forward.
	The patient decides to withdraw from the study.	Patient and tooth will be censored and the last observation carried forward.
Study	One to four patient(s) show adverse events related to treatment or material	Counteractive measures will be taken and events documented.
		Patient and tooth will be censored and the last observation carried forward. The study will be interrupted.
	More than four patients show adverse events or one patient shows a severe adverse event related to treatment or material	Counteractive measures will be taken and events documented.
		The study will be terminated. All patients and available teeth will be marked as censored and the last observation carried forward.

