### Outcomes

Outcomes will be assessed by the treating dentists or study nurses. The primary outcome of the study will be success (not requiring any re-intervention). Secondary outcomes will include survival (not requiring extraction), restoration integrity, assessed via modified USPHS-criteria [13], patients’ subjective assessment of the treatment using a visual analogue scale (for stepwise excavation, assessments will be performed twice and mean visual analogue scale results will be calculated), dentists’ and parents’ subjective assessment of the treatment using grades 1 (very good) to 6 (very bad) and initial and follow-up treatment costs (calculated by combining costs for staff, as assessed by time required for the procedures and the number of personnel involved, and costs for transportation of patients or materials).

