**Flowchart of the study.**

If pulpal exposure occurs during excavation, a pulpotomy will be attempted. This will be provided according to dental routine, using ferric-sulfate for hemostasis and a calcium hydroxide dressing. Teeth with amputated pulps will be restored via stainless steel crowns if necessary. If no amputation is possible, teeth will be extracted. All retained teeth will be followed up on regardless of the treatment arm.

Data collection will be performed via case reports forms. The following data will be collected after the initial or second-step treatment:Anesthetic and restorative material used,Patients’ cooperation (1 to 4) [24],Subjective assessment of patient (visual analogue scale),Subjective assessment of parent (grade 1 to 6),Subjective assessment of dentist (grade 1 to 6),Transportation time and costs, andTime, staff and material required for treatment.

During follow-up examinations, the following parameters will be assessed:Tooth retreated at another clinic (yes or no),Tooth exfoliated (yes or no),Sensitivity and symptoms, andRestoration integrity [22].

If retreatments are required, the cost of these will be assessed as well. Retained, retreated teeth will be followed up on to assess the survival of these teeth regardless of retreatment. A summary of performed procedures and recorded data can be found in Table 2.

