### Data analysis and statistical evaluation

The statistical evaluation will be performed using SPSS 20.0. Descriptive statistics will be calculated according to distribution of data. Log rank tests will be used to compare success and survival between groups, with effects of possible confounders (age, gender, dental anxiety, cooperation, use of local anesthetics, caries risk, dental arch, first or second molar, surfaces and center) being assessed. Moreover, we will use two-sided independent t tests or Mann-Whitney U test (to compare visual analogue scale results and costs) as well as chi-square tests (to compare restorative integrity and subjective grading of treatments).

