#### Adverse events and code-breaking

The performed procedures, despite not being used by all dentists worldwide, can be regarded as clinical routine, especially for treating children [25,26]. We therefore expect adverse or severe advents to be similar to those associated with routine treatment. Specific study-related adverse or severe events will be allergy or severe reaction to a study material used (local anesthetics, bonding and/or compomer) or rare, uncommon reactions (unexpected bleeding, unexpected severe pain and/or uncontrollable anxiety) to or during the performed interventions. Any adverse event to treatments provided within the study will be investigated and reported to the ethics committee. In case of serious adverse events requiring un-blinding, code-breaking is possible. If the investigation is terminated prematurely or suspended, the principal clinical investigator (FS) will promptly inform the clinical investigators of all centers. Additionally, the ethics committee will also be informed immediately.

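### Table 3 censors a tooth after a treatment-related adverse event: this is informative for the success comparison and conflicts with the Complication row and the follow-up rules

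*Protocol article*

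**What the plan says.** Success, meaning that no re-intervention is needed, is the primary outcome (Outcomes). The analysis is by log-rank test: "Log rank tests will be used to compare success and survival between groups" (Data analysis and statistical evaluation).

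Table 3, which covers the handling of loss to follow-up, has a patient-level row headed "Adverse or serious adverse events related to treatment or material". Its consequence, besides countermeasures and documentation, is: "Patient and tooth will be censored and the last observation carried forward". Separate rows cover children who cannot be examined and children who withdraw.

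The tooth-level Complication row of the same table says: "Complications leading to tooth loss will be counted as non-survival". It continues: "Teeth with complications which allow the retention of the tooth will be count as non-success". Surviving teeth under that row stay in follow-up.

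The section Adverse events and code-breaking defines study-related events as allergy or severe reaction to a study material, or "rare, uncommon reactions (unexpected bleeding, unexpected severe pain and/or uncontrollable anxiety) to or during the performed interventions".

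The Missing data text treats drop-outs as failures under intention-to-treat. Intervention and data collection says "All retained teeth will be followed up on regardless of the treatment arm", and later that retained, retreated teeth are followed for survival. The Discussion says that retreated teeth stay in the analysis.

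**The concern.** A log-rank test assumes that a tooth censored at a given time has the same later risk as the teeth still under observation in its arm. Leaving the risk set because the study treatment caused a reaction does not meet that assumption. Some of the listed reactions, such as unexpected severe pain or a reaction to the bonding agent or compomer, could plausibly lead to re-intervention, which is the endpoint itself.

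The documents also give several values of the primary outcome for the same tooth. If the choice between them is made after the event, in an open-label second step, it becomes a discretionary decision on the primary outcome. Censoring would also end the tooth's contribution to the survival analysis, although the Discussion presents long-term follow-up of retreated teeth as a strength of the design.

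**Working it through.** The plan gives no figure for the effect of this rule, so there is none to reproduce. The check sets the rules side by side and then bounds the effect.

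**1. One tooth, several rules.** Take a tooth with unexpected severe pain after an excavation, which is then re-restored and retained.

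| Place | Primary-outcome value |
|---|---|
| Table 3, Complication row | Non-success; follow-up continues |
| Table 3, adverse-event row | Censored at the last observation |
| Missing data text | Non-success, if the child is classed as a drop-out |
| Intervention and data collection; Discussion | Tooth followed; retreated teeth not excluded |

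Nothing says which prevails. Carrying the last observation forward adds to the ambiguity. Censoring ends time at risk, whereas carrying a status forward literally would extend it.

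**2. Balance between arms.** Allocation is revealed after the six-month recall. The first excavation and restoration therefore precede it in both arms, and events at that step are unrelated to allocation. Afterwards only the stepwise arm has a planned second excavation and restoration. For an event at that second step the last observation is the recall, so the tooth would contribute essentially no follow-up after allocation. Unequal exposure to the rule is thus plausible, but the documents give no event rates.

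**3. How many patients.** Table 3 terminates the study when more than four patients have adverse events, or when one has a severe one. At most k = 4 patients can therefore be affected before termination.

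**4. Worst-case size.** Inputs: 300 recruited, assumed equally split (n = 150 per arm; the ratio is not stated), or the 114 per group of the sample-size section. All four patients are placed in one arm and all are true failures. Failure rates are assumptions.

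- True rate f/n; rate under censoring, approximated as (f − k)/(n − k), which treats the teeth as leaving at about allocation.
- At 20% failing: 30/150 = 20.0% against 26/146 = 17.8%, a difference of 2.2 points.
- At 6% failing (the stepwise failure figure of one 16-month trial in the protocol's Table 1): 9/150 = 6.0% against 5/146 = 3.4%, a difference of 2.6 points.
- Simple bound k/n: 4/150 = 2.7 points; 4/114 = 3.5 points. For one patient: 1/150 = 0.7 and 1/114 = 0.9 points.

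**5. Scale.** At 20% failing in each arm of 150, the standard error of the difference is √(2 × 0.2 × 0.8 / 150) = 4.6 points. The worst-case shift of 2.2 points is about half of that.

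**6. The opposite reading.** If the drop-out sentence governs and none of the four would have needed retreatment, up to four non-failures in one arm count as failures. The simple bound is the same 4/150 = 2.7 points, in the other direction.

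These are crude proportions. In the log-rank test a tooth stays at risk until it is censored, so later censoring has a different and generally smaller effect.

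**The case against.** The strongest reply is that the two rows work at different levels. The Complication row deals with the tooth and counts harm to it as failure; the adverse-event row deals with the patient. Most listed reactions (allergy, bleeding, anxiety, transient pain) are not re-interventions and so not failures. The procedural reactions are described as rare, and the stopping rows keep the number at four or fewer. If severe pain were classed as a severe adverse event, the first case would end the trial. The follow-up sentence quoted from Intervention and data collection closes a paragraph on pulp exposure and speaks of treatment arm, not adverse events.

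Much of this stands. A reader might infer that Table 3 removes excavation harm from the failure count outright. The documents do not support that, because the Complication row still counts it. A reader might also infer that the carried-forward status is always a success, or that the affected teeth are mostly in the stepwise arm. Table 3 says only that the last observation is used, no rates are given, first-step events precede allocation, and retreatments can occur in either arm.

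What does not stand is the idea that the levels settle the matter. The adverse-event row censors the tooth as well as the patient, and severe pain leading to retreatment belongs to both rows. Even where no retreatment follows at once, the tooth is taken out of observation for a treatment-caused reason while the child remains examinable. The later statements on retreated teeth, in the same section and in the Discussion, do not depend on the pulp-exposure paragraph.

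**Conclusion.** The point holds as a badly fixed analysis rule. Censoring for a treatment-related adverse event is informative for the primary comparison. It gives a different outcome from the Complication row when one event fits both, and it does not agree with the Missing data text or with the stated follow-up of retained and retreated teeth.

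The size is limited: four patients at most before termination, and about 2 to 3 percentage points at an assumed 150 per arm if all four are in one arm, all are true failures and none is caught by the Complication row. The relative effect is larger if failures are rare. Some imbalance after month six is plausible from the design, but the documents do not establish that one arm is favoured. Severity is moderate to minor.

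**What to change.** Reconcile the Table 3 rows with the Missing data text, Intervention and data collection, and the Discussion, and state one analysis rule:

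- An adverse event is not in itself a reason for censoring.
- Any re-intervention on the study tooth counts as non-success on its date, and as non-survival if the tooth is extracted, whether or not it followed an adverse event.
- Otherwise the tooth stays at risk.
- A tooth is censored only when the child is no longer examined, at the last examination.
- Adverse events are reported separately by arm, with those at the first step shown apart from those after allocation.

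This concerns the analysis only and leaves clinical handling and the stopping rows as they are. It is a wording change that adds no scheduled visits. Centres that read the adverse-event row as ending follow-up would need to be told to keep seeing those few children while their families agree. The downside is that success rates may look slightly lower.

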### Objectives and hypotheses

The study aims at comparing the success (the probability of not requiring any re-interventions) and the survival (the probability of not requiring tooth removal) of selectively excavated versus stepwise excavated vital, non-symptomatic deciduous molars with deep lesions. In addition, we assess the restoration integrity of selectively excavated versus stepwise excavated deciduous molars, evaluate the preference of patients, parents and dentists for one of both strategies, and comparatively assess the costs associated with each strategy.

Our primary hypothesis is that success rates differ significantly between selectively excavated and stepwise excavated teeth. Secondary hypotheses are that restoration integrity is assumed to significantly differ between selectively excavated and stepwise excavated teeth. Moreover, we hypothesize that patients’, parents’ and dentists’ preference is significantly different for selectively excavated versus stepwise excavated teeth. Eventually, both initial and long-term costs of excavation methods are supposed to significantly differ.

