## Methods/Design

### Overview

The planned study is a secondary care-based prospective, multicenter, two-arm parallel-group, randomized controlled trial at three pediatric university dental clinics in Germany: the Charité - Universitätsmedizin Berlin, the Ernst-Moritz-Arndt University Greifswald and the RWTH University of Aachen. We plan to enroll 300 patients with one or more deeply carious, sensitive and non-symptomatic deciduous molar. One molar per patient will be randomly allocated to receive one of two treatments (selective or stepwise excavation). The total follow-up time will be three years after completion of the initial treatment. Success, survival and restoration integrity will be assessed after one, two and three years. Patients’, parents’ and dentists’ preference will be assessed after each treatment using visual analogue or Likert rating scales. Costs will be assessed for the initial and follow-up treatments and will be based on a micro-costing approach. The study has been approved by the ethics committee of the Charité - Universitätsmedizin Berlin (approval number: EA4/057/14), the Ernst-Moritz-Arndt University Greifswald (approval number: BB 112/14) and the RWTH University of Aachen (approval number: EK 283/14). The study is registered at Clinicaltrials.gov (identifier: NCT02232828).

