### Sample size

The required sample size was calculated based on the primary outcome parameter, success (see below). We anticipate a hazard ratio of 1.3 [21] of stepwise excavated compared with selectively excavated teeth. If α = 0.05 and 1-β = 0.9, a sample size of n = 66 per group is required. Assuming an annual drop-out rate of 20%, 114 patients per group will be required. The total required sample size would thus be n = 228. To allow possible subgroup analyses, a total of 300 patients will be recruited (n = 100 per center).

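### Table 3's last-observation-carried-forward rule is not limited to any outcome, so in effect it acts on restoration integrity and biases that secondary chi-square comparison

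*Protocol article*

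**What the plan says.** The protocol article's Table 3 (Handling of loss to follow-up) states for a child who cannot be examined: "Patient and survived tooth or teeth will be censored and the last observation carried forward". For withdrawal and for treatment-related adverse events it states: "Patient and tooth will be censored and the last observation carried forward". For exfoliated teeth: "The last observation will be carried forward". No row says which outcome the rule covers.

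The section on data analysis assigns the tests: "Log rank tests will be used to compare success and survival between groups", and "chi-square tests (to compare restorative integrity and subjective grading of treatments".

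Restoration integrity carries its own hypothesis in Objectives and hypotheses: "Secondary hypotheses are that restoration integrity is assumed to significantly differ between selectively excavated and stepwise excavated teeth". The Overview gives the schedule: "Success, survival and restoration integrity will be assessed after one, two and three years".

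The Sample size section supplies the one relevant rate: "Assuming an annual drop-out rate of 20%, 114 patients per group will be required". The Missing data text foresees unequal loss between groups. Its remedy, counting drop-outs as failures, is worded for success and survival only.

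**The concern.** Table 3 pairs two instructions, censor and carry forward. A log-rank test needs only the first. A chi-square test on scores cannot use the first, so only the second can operate on restoration integrity.

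An unrepaired restoration tends to get worse with time. A score from month 12 entered as the month-36 score therefore flatters the restoration, and the flattery grows with the number of children lost. Three consequences follow:
- late integrity is overstated in both arms;
- the test counts carried values as if those children had been examined;
- the arm that loses more children looks better, whatever the treatment does.

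Restoration quality over sealed carious dentin is one of the doubts that the Background and Discussion give as a reason for the trial. This comparison should not turn on who stopped attending.

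**Working it through.** **Plan's own figure.** The plan gives no figure for carried-forward scores. Its 114 per group reproduces as 66 × 1.2³ = 114.05, so the 20% yearly loss is meant to run over three years. (A 20% yearly loss leaves 0.8³ = 51.2%, and 66/0.512 = 129. That is a separate matter, and nothing below rests on it.)

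**Inputs.** From the protocol: 20% loss a year, scores at 1, 2 and 3 years, chi-square test, 300 children. Assumed: 1:1 allocation (150 per arm), a constant yearly probability *p* that a restoration stays intact, loss at yearly rate *d* that is independent of restoration state, and an intact/not intact outcome. Exfoliated teeth and the new restoration placed in the stepwise arm at six months are left out.

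**Two readings of the first score.** The Overview puts the first score at 12 months. Table 2 also marks clinical outcomes at the six-month visit, so a six-month score may exist.

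*Reading A, first score at 12 months.* Among children with at least one score, the carried-forward proportion intact at month 36 is

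d·p + (1−d)d·p² + (1−d)²·p³.

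- Carried share at d = 0.2: 1 − 0.8² = 36%.
- p = 0.90: 0.180 + 0.1296 + 0.4666 = 77.6%.
- p = 0.85: 0.170 + 0.1156 + 0.3930 = 67.9%.
- Apparent gap: 9.8 points.

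*Reading B, a six-month score exists and loss runs from then.* With r = 1−d, the proportion is

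(1−r^0.5)·p^0.5 + (r^0.5−r^1.5)·p + (r^1.5−r^2.5)·p² + r^2.5·p³.

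- Carried share at d = 0.2: 1 − 0.8^2.5 = 42.8%, so about 86 of 150 are examined at month 36.
- p = 0.90: 0.1002 + 0.1610 + 0.1159 + 0.4173 = 79.4%.
- p = 0.85: 0.0973 + 0.1521 + 0.1034 + 0.3516 = 70.4%.
- Apparent gap: 9.0 points.

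*True gap:* 0.9³ − 0.85³ = 72.9% − 61.4% = 11.5 points. Carrying forward removes about 15% of it (A) to 22% (B) when loss is equal.

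**No true difference, unequal loss.** Rejection is that of the two-sided 5% pooled test of two proportions:

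1 − Φ[(1.96·se₀ − δ)/se₁] + Φ[(−1.96·se₀ − δ)/se₁],

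with se₀ pooled and se₁ unpooled. The number per arm is 150(1−d) in A and 150 in B.

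| Reading | p in both arms | Yearly loss | Apparent % intact | False gap (points) | Rejection |
|---|---|---|---|---|---|
| A | 0.90 | 15% v 25% | 76.5 v 78.7 | 2.2 | 6.9% |
| A | 0.85 | 15% v 25% | 66.3 v 69.3 | 3.0 | 7.8% |
| B | 0.90 | 15% v 25% | 77.9 v 80.9 | 2.9 | 9.6% |
| B | 0.85 | 15% v 25% | 68.4 v 72.4 | 4.1 | 12.0% |
| A | 0.90 | 10% v 30% | 75.3 v 79.7 | 4.4 | 12.4% |
| A | 0.85 | 10% v 30% | 64.7 v 70.8 | 6.0 | 16.5% |
| B | 0.90 | 10% v 30% | 76.3 v 82.2 | 5.9 | 24.0% |
| B | 0.85 | 10% v 30% | 66.2 v 74.3 | 8.1 | 33.5% |

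Last row in full: se₀ = 0.0528, se₁ = 0.0526, (1.96 × 0.0528 − 0.0811)/0.0526 = 0.43, and 1 − Φ(0.43) is about 0.335. Under the same assumptions a test on examined children only stays at 5%.

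**Direction is not fixed.** If the better arm (p = 0.90) loses 30% a year and the worse arm (p = 0.85) loses 10%, the 11.5-point gap appears as 15.0 (A) or 16.0 (B). With the losses swapped it appears as 4.6 (A) or 2.1 (B).

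**The case against.** The target is inferred. Table 3 speaks of censoring, success and survival, and never of restoration scores. Its phrase could mean only that the status at the last visit is kept as the censored record. The analysis section does not say which visit the chi-square test uses, and an article may leave such detail to a fuller document. This stands as a limit on certainty. It does not remove the point: the article states both the rule and the test, exempts no outcome, and gives no other rule for restoration scores.

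Three stronger readings are tempting, and the documents do not support them:
- **Larger effects.** A reader might take 1 − 0.8³ = 48.8% of scores as carried forward and enter every child lost in year one as intact. That would remove about a third of the true gap and put false rejection at 15–20% and 44–61%. No such score is planned: Table 2 leaves clinical outcomes blank at the first step, and restoration integrity is listed only under follow-up examinations. Allocation is revealed only after the six-month examination, so earlier loss cannot be caused by the arm.
- **An extra visit in the stepwise arm.** The second excavation follows the six-month examination and shares a column with it in Table 2. It may take place at a visit that both arms attend. Unequal loss is therefore possible, and the Missing data text foresees it, but the splits used here are assumptions.
- **Real differences always shrink.** The last calculation shows that they can grow. Nominal power can also rise. For assumed year-3 defect rates of 20% v 10%, equal 20% loss and a six-month score, it is about 55% with carried values and 45% in examined children.

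It is also fair that time to first unacceptable score is a different estimand, and that a table of examined children is itself biased if loss depends on restoration state.

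**Conclusion.** The concern holds for a secondary outcome and does not touch the log-rank analyses of success and survival. Read as written, the plan lets old restoration scores stand in for late ones in a test that treats them as observed. The harm is bias and overstated precision, in a direction that depends on which arm loses more children.

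Under the stated assumptions, a 15–22% shrinkage at equal loss is modest. Moderate imbalance raises the false-positive rate somewhat above 5%, and strong imbalance raises it to several times 5%. Only the 20% yearly loss is the protocol's own figure. Deterioration rates, unequal loss, arm size and independence of loss from restoration state are assumed. Two omitted features would change the size. Teeth expected to exfoliate within 18 months are excluded but follow-up runs three years, so exfoliation may add carried scores. In the stepwise arm, a carried six-month score would describe a restoration since replaced.

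**What to change.** 1. In Table 3, limit the rule to success and survival and word it as censoring at the last examination. The exfoliation row now gives carrying forward alone and needs the same change.
2. Delete last observation carried forward for restoration integrity.
3. Analyse the observed scores at 1, 2 and 3 years with a longitudinal ordinal model. Time to first unacceptable score, with censoring, is an alternative if that is the question wanted.
4. Show the 36-month table of examined children as descriptive, with the number examined per arm.
5. Add a sensitivity analysis for restoration scores not missing at random.

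The cost is a change of wording and a little more analysis work. Visits and data collection stay as they are. The interval at 36 months will be wider, which reflects the number of children actually examined. Whether drop-outs are failures (Missing data text) or censored (Table 3) in the log-rank outcomes is a separate conflict and also needs settling.
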